**Phase 1**			
Quantitative study (Cross-sectional study)	Investigate happiness (Identifying happiness levels and key demographic and occupational variables that contribute to or detract from happiness in the workplace)	Checklist of demographic characteristics and occupational features Oxford Happiness Questionnaire	Nurses

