### 2.1 Study 1: Cross‑sectional survey

This study adopts a sequential explanatory mixed‑methods design. The rationale for this design is that the quantitative phase (cross‑sectional survey) will first identify the levels and correlates of happiness among nurses. Subsequently, the qualitative phase (semi‑structured interviews) will be used to explain, elaborate on, and provide contextual depth to the quantitative findings. This design is well‑suited to our aim of developing evidence‑based, actionable strategies, as the qualitative data will help interpret statistical patterns and uncover the mechanisms underlying the observed relationships. The primary aim of the first phase of this study is to conduct a cross-sectional investigation into the levels of happiness among nurses working in hospitals. This quantitative approach will involve the administration of standardized surveys to assess various dimensions of happiness, including emotional, social, and cognitive components. By collecting data from a diverse sample of nurses across different hospital settings, the study seeks to quantify happiness levels and identify factors that contribute to or hinder happiness in the workplace. The findings will provide a comprehensive overview of the current state of happiness among nurses, highlighting areas that require attention and intervention. To achieve this aim, the following research hypotheses will be tested:

There is a significant relationship between demographic variables (age, gender, marital status, family income) and nurses’ happiness scores.There is a significant relationship between occupational variables (work experience, employment status, salary satisfaction, overtime hours, shift work) and happiness scores.Nurses who participate in recreational and cultural activities (either at the workplace or outside of it) have higher happiness scores compared to nurses who do not participate in such activities.Satisfaction with physical and mental health has a significant positive correlation with nurses’ happiness scores.A regression model encompassing demographic and occupational variables will be able to significantly predict a portion of the variance in nurses’ happiness scores.

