#### 2.1.5 Data collection.

Data will be collected using the following instruments:

A. self-design checklist including demographic characteristics and occupational features.B. The standard Oxford Happiness Questionnaire, which will be sent to participants online.

**A. Checklist of demographic characteristics and occupational features:** This checklist will include demographic characteristics and occupational features.

The demographic section will cover: Age, Gender, Number of children, Marital status, Educational background, Spouse’s employment status, Type of housing, Family income, Engagement in recreational or cultural activities, Satisfaction with physical health, Satisfaction with mental health.

The occupational features section will include: Official position of nurses, Employment status, Current department of the workplace, Level of interest in nursing at present, Satisfaction with salary, Number of overtime hours, Shift work, Engagement in recreational activities at the workplace.

**B. Oxford Happiness Questionnaire:** The Oxford Happiness Questionnaire consists of 29 items divided into six subscales: self-esteem, life satisfaction, efficiency, positive mood, sense of control, and mental health. Respondents will answer items on a six-point Likert scale ranging from “strongly disagree” to “strongly agree.” The scoring for the six scales ranges from 1 to 6, leading to a total score that ranges from 29 to 174. A higher score indicates greater happiness. The total score will be classified into three levels: less than 100 indicates low happiness, scores between 101–131 indicate medium happiness, and scores above 132 indicate high happiness [24,25]. The validity and reliability of the Persian version of the questionnaire have been confirmed in previous studies, with a reported Cronbach’s alpha of over 0.90 [24–26].

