#### 2.1.8 Statistical analysis.

In the first phase of the study, data will be analyzed using SPSS-24 and STATA/MP software. To account for the two-stage sampling design and potential clustering effects (nurses nested within hospitals), linear mixed-effects models will be employed with ‘hospital’ included as a random intercept. This approach will provide robust standard errors and correct estimates of variance. The intra-class correlation coefficient (ICC) will be calculated to assess the degree of clustering. For categorical variables, Rao-Scott chi-square tests will be used. A significance level of 0.05 will be maintained for all tests. The extent and pattern of missing data will be assessed using Little’s MCAR test. Data are assumed to be Missing at Random (MAR). Instead of mean imputation, Multiple Imputation by Chained Equations (MICE) will be used to handle missing values in both demographic and outcome variables, generating 20 imputed datasets. The results from these datasets will be pooled using Rubin’s rules. A sensitivity analysis will be conducted by comparing results from the complete-case analysis with those from the multiple imputation approach to ensure robustness.

The first phase of this study, a cross-sectional survey of happiness among nurses in hospitals affiliated with Mazandaran University of Medical Sciences, aims to provide a comprehensive understanding of the factors influencing nurses’ well-being. By employing standardized instruments, including the Oxford Happiness Questionnaire, this phase will quantify happiness levels and identify key demographic and occupational variables that contribute to or detract from happiness in the workplace. The findings are expected to highlight critical areas for intervention, which could lead to improved job satisfaction and overall well-being among nurses. Ultimately, this phase will lay the groundwork for subsequent qualitative research, facilitating a deeper exploration of the lived experiences of nurses and informing targeted strategies to enhance their happiness in the profession.

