#### 2.2.2 Participants.

The participants will consist of professional nurses employed in the selected hospitals, ensuring a representative sample of perspectives from different nursing units. Participants for the qualitative phase will be purposively selected from those who completed the survey. Selection will be based on their happiness scores (e.g., nurses with very low, moderate, and very high scores) and key occupational variables (e.g., shift work, overtime hours, satisfaction with salary). This ensures that the qualitative sample is directly informed by, and linked to, the quantitative results.

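### Phase 1 can describe happiness among nurses, but its only outcome does not support the stated aim about happiness at work or the promised emotional, social and cognitive components

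*Protocol article*

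**What the plan says.** Three places in the protocol article set the Phase 1 aim at happiness at work:

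- Table 1, Phase 1 row: "Identifying happiness levels and key demographic and occupational variables that contribute to or detract from happiness in the workplace".
- Section 2.1: the survey is to "quantify happiness levels and identify factors that contribute to or hinder happiness in the workplace".
- Section 2.1.8, closing paragraph, in a sentence that names the Oxford Happiness Questionnaire: "identify key demographic and occupational variables that contribute to or detract from happiness in the workplace".

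Section 2.1 also says that the survey will "assess various dimensions of happiness, including emotional, social, and cognitive components". These are the three parts of the definition of happiness given in section 1.2, where the social part concerns relationships and social support.

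Section 2.1.5 names two instruments: a self-designed checklist and the Oxford Happiness Questionnaire. The questionnaire has "29 items divided into six subscales: self-esteem, life satisfaction, efficiency, positive mood, sense of control, and mental health", and a total score from 29 to 174.

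For Phase 2, section 2.2 makes workplace and professional happiness the primary question. Section 2.2.2 draws interviewees from the survey respondents: "Selection will be based on their happiness scores (e.g., nurses with very low, moderate, and very high scores"; the same sentence goes on to add key occupational variables. Section 2.2.7 ends with a joint display that compares interview themes with the statistical findings.

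**The concern.** The outcome that is measured and the outcome that the aim names are not the same. The subscale names describe a person's happiness in general. A nurse may be content in private life and unhappy at work, or the reverse, and nothing collected in Phase 1 would tell the two apart.

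Two things are at stake.

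- **What Phase 1 reports.** Section 2.1 tests marital status and family income, and the checklist also covers children, the spouse's employment and housing. Under the wording of Table 1 and section 2.1.8, an association of any of these with the total score would be presented as a contributor to happiness at work. The data would show only a correlate of general happiness among nurses.
- **What the integration means.** The design is sequential explanatory, so the interviews are meant to explain the survey result. If the survey side of the joint display concerns general happiness and the interview side concerns work, an apparent contradiction may reflect only the change of construct. The display feeds directly into the recommended strategies.

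**Working it through.** This point is settled by setting the texts side by side. No figure in the plan depends on it: the initial sample size reproduces, (1.96 × 17.28 / 2)² = 16.9344² = 286.8, rounded up to 287, and so does the score range, 29 × 1 = 29 to 29 × 6 = 174. Neither would change with the label on the construct.

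**Step 1. What the aim names and what is measured**

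| Element of the Phase 1 aim | Where stated | Phase 1 measure available |
|---|---|---|
| Level of happiness among nurses | 2.1, Table 1 | Questionnaire total: yes |
| Five hypotheses, all on happiness scores | 2.1 | Questionnaire total: yes |
| Happiness specifically at work | Table 1, 2.1, 2.1.8 | None |
| Emotional, social and cognitive components | 2.1 | Six subscales, with no stated mapping |

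**Step 2. The subscales.** Section 2.1.5 lists "six subscales: self-esteem, life satisfaction, efficiency, positive mood, sense of control, and mental health". Named as work-specific: 0 of 6. Named as social: 0 of 6. Positive mood might be placed under an emotional component and life satisfaction under a cognitive one, but the article does not do so, and no listed name corresponds to the social part as section 1.2 defines it.

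**Step 3. The checklist.** It lists 11 demographic and 8 occupational entries, 19 in all. None is a rating of happiness at work. The nearest are current interest in nursing and satisfaction with salary. Both sit among the occupational features, and the second hypothesis uses salary satisfaction as an explanatory variable. Neither is available as a workplace outcome.

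**Step 4. The link to Phase 2.** Interviewees are chosen partly on the questionnaire score (2.2.2) and then asked about happiness at work (2.2). The themes are compared with the Phase 1 statistics (2.2.7). That the selection score and the interview topic are different constructs is an inference from reading 2.1.5, 2.2 and 2.2.2 together; the article does not say it.

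**Step 5. Size.** The documents give no correlation between the questionnaire total and happiness at work, so how far one could stand in for the other cannot be stated.

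**The case against.** The strongest reply is that most of Phase 1 is worded correctly. Section 2.1 gives the primary aim as the level of happiness among hospital nurses, the abstract's objective is the current state of happiness among nurses, and all five hypotheses take happiness scores as the outcome. Studying occupational correlates of general happiness in a workforce is a legitimate design, and the interviews cover the workplace construct. All of this stands. A reader might infer that Phase 1 cannot answer its question at all; the documents do not support that.

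A reader might also infer that section 2.2.2 treats the score as a measure of workplace happiness. It does not. It speaks only of happiness scores, and it selects on shift work, overtime and salary satisfaction as well; section 2.2.5 adds variation by age, gender, specialty and shift type. In a purposive sample, a nurse who is happy at home and unhappy at work is a useful informant, and section 2.2 asks about individual as well as organizational factors. This disposes of any claim that the selection rule is itself wrong. It does not remove the mismatch in the joint display.

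The abstract's conclusion on workplace happiness is weak evidence too, since it covers the whole study, interviews included.

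Finally, the 29 items are not reproduced, and efficiency is not defined. Some items may touch on work or relationships. So what can be said is that no subscale is named as work-specific or social and that no mapping is given, not that the questionnaire has no such content. Even so, an item or two inside a total score would not yield a workplace outcome or a reportable social component.

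**Conclusion.** The concern holds in a limited form. Phase 1 supports statements about the level of happiness among nurses and about its demographic and occupational correlates, including all five hypotheses. It does not support the workplace-specific part of the aim in Table 1, section 2.1 and section 2.1.8, and it gives no stated route to the three components promised in section 2.1.

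The analysis can run as planned and no number changes. What changes is the claim that may be attached to the results, and how the joint display is read. The conclusion rests on one assumption: that the subscale names in section 2.1.5 fairly describe what the questionnaire measures. The article itself never labels the instrument as general or as work-related.

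It should be corrected before recruitment. The article says that recruitment has not begun. Once the survey has closed, only relabelling remains possible.

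**What to change.** 1. In Table 1, section 2.1 and section 2.1.8, state the Phase 1 outcome as general happiness among nurses, and its results as demographic and occupational correlates of that score. Leave statements about happiness at work to Phase 2.
2. In section 2.1, replace the emotional, social and cognitive components with the six subscales, or state which subscales or items represent each component. If none represents the social one, say so.
3. In section 2.2.7, add a sentence that the survey side of the joint display refers to general happiness and the interview side to happiness at work, so that disagreement is read with this in mind.
4. Only if a quantitative workplace claim is to be kept: add a brief item on overall happiness at work to the checklist before recruitment, report it as a secondary outcome, and consider it alongside the existing score and occupational criteria when choosing interviewees.

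Items 1 to 3 cost wording only, and a narrower claim for the questionnaire total. Item 4 costs one extra question for each respondent; its drawback is that a single item is not formally validated, so its results would need to be reported with that caution. Item 4 is optional: items 1 to 3 are enough to make the plan consistent.

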### 2.2 Study 2: Qualitative study

The second phase of this study will employ a qualitative approach to gain deeper insights into the experiences and perceptions of nurses regarding happiness in their work environment. Through in-depth interviews, this phase aims to explore the nuanced factors that influence happiness, such as workplace culture, support systems, and personal coping mechanisms. By capturing the voices and narratives of nurses, the qualitative study will identify specific strategies that can be implemented to enhance happiness and well-being in the nursing profession. This dual approach, combining quantitative and qualitative methods, will provide a holistic understanding of happiness in nursing and inform effective interventions to promote a more positive work environment. To guide this phase, the following primary and secondary qualitative research questions will be addressed:

The primary qualitative research question is: What are the lived experiences and perceptions of nurses regarding happiness in the workplace, and what factors, from their perspective, contribute to or hinder professional happiness?

Secondary Qualitative Research Questions include:

How do nurses define and describe happiness in the workplace?What individual factors (e.g., mental health, lifestyle, coping skills) from the nurses’ perspective influence their happiness?What organizational and workplace factors (e.g., organizational culture, managerial support, collegial relationships, human resources) are experienced as facilitators or barriers to professional happiness?From the nurses’ perspective, what is the impact of happiness on professional performance, quality of patient care, and interactions with colleagues?What practical strategies and solutions (at the individual, team, and managerial levels) are proposed to promote happiness in the nursing work environment?What structural or cultural barriers within healthcare organizations impede the realization of professional happiness among nurses?

#### 2.2.1 Study setting.

The qualitative study will be conducted in various hospitals affiliated with Mazandaran University of Medical Sciences, providing a rich context for understanding the diverse experiences of nurses.

#### 2.2.2 Participants.

The participants will consist of professional nurses employed in the selected hospitals, ensuring a representative sample of perspectives from different nursing units. Participants for the qualitative phase will be purposively selected from those who completed the survey. Selection will be based on their happiness scores (e.g., nurses with very low, moderate, and very high scores) and key occupational variables (e.g., shift work, overtime hours, satisfaction with salary). This ensures that the qualitative sample is directly informed by, and linked to, the quantitative results.

#### 2.2.3 Inclusion criteria.

Participants must meet the following criteria:

a) Willingness to share their experiences regarding happiness in the workplace.b) Ability to engage in the study with maximum diversity in terms of age, gender, and nursing specialties**.**

#### 2.2.4 Exclusion criteria.

Participants will be excluded if they:

a) Are unwilling to participate or share their experiences during the interviews.

#### 2.2.5 Data collection and interview procedures.

**A. Semi-structured interviews:** This qualitative exploratory-descriptive study aims to uncover the perspectives and experiences of professional nurses regarding happiness in the workplace. The study seeks to elucidate nurses’ experiences and viewpoints on happiness, its impact on their performance, and the identification of ways to enhance professional happiness in healthcare settings. To achieve this, semi-structured interviews will be conducted, with questions formulated based on the study’s objectives and a review of relevant literature. Preliminary analysis of the quantitative data will be used to refine the semi‑structured interview guide. For example, if the survey reveals that nurses with high overtime hours report significantly lower happiness, the interview questions will explore the specific experiences and contextual factors underlying this finding. The interviews will explore and understand the nurses’ experiences and perspectives on happiness and its implications for their professional performance. Insights, suggestions, ideas, and potential solutions will be gathered to contribute to enhancing professional happiness in healthcare environments. Data saturation will be ensured by continuing interviews until no new information emerges, thereby ensuring comprehensive coverage of a wide range of perspectives and experiences related to the study’s objectives. To maintain the validity and reliability of the data, interviews will be conducted in a tranquil environment, with note-taking and audio recording to ensure accuracy and thorough immersion in the data.

To ensure the validity and reliability of the data in the qualitative research, the study will incorporate measures based on the criteria established by Guba and Lincoln [28]. Four criteria will be utilized as standards of scientific rigor: credibility, transferability, dependability, and confirmability.

**Credibility** will be established through member checking and prolonged engagement, fostering rapport and understanding of their experiences.**Transferability** will be achieved by employing maximum diversity in sampling techniques, allowing findings to be applicable across various contexts. Operationalization of maximum diversity includes variation based on age (age groups: 20–30, 31–40, 41–50+), gender (male and female), nursing specialty (e.g., emergency, ICU, medical-surgical), and shift type (fixed, rotating, night shift). Despite using snowball sampling as an auxiliary technique, the primary sampling strategy will be purposive sampling driven by the quantitative results to ensure this diversity from the outset.**Dependability** will be ensured by documenting similar situations for participants, promoting consistency in findings. An audit trail will be maintained, documenting all analytical decisions and methodological choices.**Confirmability** will be enhanced through reflexive memoing and external review by experts and integrating supplementary opinions into the data analysis process.

Furthermore, to ensure the reliability of the data, the study will utilize methods such as note-taking and recording personal reflections to enhance objectivity. The use of MAXQDA 10 software for text coding will demonstrate a systematic and rigorous approach to data management and analysis, reinforcing the reliability of the findings [28]. In conclusion, this study will utilize a rigorous methodology with semi-structured interviews to explore nurses’ professional happiness. The goal is to produce reliable findings that enhance the well-being and performance of nurses in healthcare settings.

### Interview implementation process

#### Interviewer identity, role, and training.

All semi-structured interviews will be conducted by the principal investigator ([name]). The interviewer has no supervisory or evaluative authority over the participating nurses, which will be clearly stated at the beginning of each interview to reduce potential power imbalance and social desirability bias. Prior to data collection, the interviewer will complete a 20-hour training workshop on qualitative interviewing techniques, including active listening, probing, reflexivity, and ethical conduct in sensitive workplace research.

#### Interview mode and approximate duration.

Interviews will be conducted face‑to‑face in a private, quiet room within the participants’ hospital such as a supervisor’s office or a meeting room to ensure confidentiality and minimize interruptions. Each interview is expected to last between 45 and 60 minutes, depending on participant engagement and the richness of the responses provided. No repeat interviews are planned; however, participants will be contacted for member checking if clarification or further elaboration on their responses is required.

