## 3. Ethics

The Research Ethics Committees of Imam- Mazandaran University of Medical Sciences Approved the study (IR.MAZUMS.IMAMHOSPITAL.REC.1402.119). Written informed consent will be obtained from all participants prior to their involvement in any study-related procedures, including both the quantitative survey and qualitative interviews. Participants will be fully informed about the purpose of the study, the voluntary nature of their participation, and their right to withdraw at any time without any negative consequences. Withdrawal will not affect their employment, education, or access to services. Confidentiality will be strictly maintained throughout the study; all personal identifiers will be removed or coded, and data will be stored securely. Data protection procedures include password-protected electronic files, limited access to authorized researchers only, and secure physical storage of any paper-based records. All data will be anonymized prior to analysis and reported only in aggregate form to prevent individual identification.

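### Listing a supervisor's office as a possible interview room works against the plan's own aim of limiting power imbalance and social desirability bias

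*Protocol article*

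**What the plan says.** All statements are in the Protocol article.

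- **Venue** (Interview mode and approximate duration). "Interviews will be conducted face‑to‑face in a private, quiet room", located in the participant's own "hospital such as a supervisor’s office or a meeting room to ensure confidentiality and minimize interruptions". The supervisor's office is the first of two examples and the meeting room is the second.
- **Safeguard** (Interviewer identity, role, and training). "The interviewer has no supervisory or evaluative authority over the participating nurses, which will be clearly stated at the beginning of each interview". The stated purpose is "to reduce potential power imbalance and social desirability bias". The interviewer's training also covers "ethical conduct in sensitive workplace research".
- **Subject matter** (section 2.2). One secondary question reads: "What organizational and workplace factors (e.g., organizational culture, managerial support, collegial relationships, human resources) are experienced as facilitators or barriers to professional happiness". Other questions ask for strategies at managerial level and for structural or cultural barriers in the organization.
- **Confidentiality** (section 3, Ethics). "Confidentiality will be strictly maintained throughout the study".

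**The concern.** The plan recognises that nurses may temper what they say when authority is close at hand, and it responds by keeping the interviewer outside the line of authority. A supervisor's office brings a visible sign of that authority back into the interview. The questions concern, among other things, "organizational culture, managerial support, collegial relationships, human resources", so some participants would be invited to criticise management while sitting in a manager's space.

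Two things are at stake. The first is candour: answers about management as a barrier could be softened, and a reluctant nurse could decline. The second is privacy of attendance: the occupant of a borrowed office could learn who was interviewed. Section 2.2.7 lets the integrated results, including the qualitative themes, shape the final recommended strategies. Under-reported management barriers could therefore carry through to the study's main product.

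**Working it through.** No arithmetic applies. The document gives no figure on this point and none from which a bias could be sized. The check is a comparison of the sections.

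1. **Venue against safeguard.** The safeguard works by separating the interview from supervisory authority. The venue text allows the interview to take place in a room that belongs to someone who holds such authority. The interviewer's opening declaration could thus be made in a supervisor's own office. It would still be true, but its reassurance would be weaker.

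2. **Venue against subject matter.** The room would matter less if the questions were neutral. Section 2.2 asks about managerial support, organizational culture and structural barriers, and the training section itself treats the topic as sensitive. The questions most exposed are those on organizational factors and barriers.

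3. **Venue against confidentiality.** The venue sentence justifies its choice of room partly by confidentiality, and section 3 promises confidentiality throughout. Under Transcription process, names, hospital names and specific units are removed or pseudonymized. That protects what was said; it does not hide who attended. Interviews are expected to last 45 to 60 minutes, so an office would be borrowed for long enough that its usual occupant could come to know of it. This is the more delicate because section 2.2.2 selects participants partly on happiness score, including very low scores, and on satisfaction with salary.

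4. **Search for something that closes the gap.**
   - No section excludes the office of the participant's own supervisor, gives the participant a choice of place, or says how attendance would be kept from a supervisor.
   - The pilot of the interview guide covers clarity, flow, cultural appropriateness and duration, not the room.
   - Member checking returns a summary of themes to the same nurses, so it cannot be relied on to bring out what they held back.
   - Reflexive memoing and external review (section 2.2.5) work on what was said.
   - No repeat interviews are planned.

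5. **Extent.** The possible effect reaches only the interviews held in such an office. That number is not fixed by the plan and could be zero. The questionnaire is sent online (section 2.1.5), so the quantitative phase is outside the concern.

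**The case against.** The strongest reply is that the operative requirement is a private, quiet room, and the office is only an illustration beside a meeting room. An investigator could follow the protocol exactly and never enter a supervisor's office. This stands, and it limits the point to one ill-chosen example.

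Secondly, a reader might infer that the plan contradicts itself. It does not: the safeguard concerns the interviewer, who lacks authority in any room. What remains is a tension between two design choices.

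Thirdly, a reader might infer that the nurse's own supervisor owns the room, is present, or is certain to learn who took part, and that answers will therefore be biased. The text says none of this. A borrowed office elsewhere in the hospital fits the wording equally well. Disclosure and loss of candour are possible results, not established ones.

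Fourthly, other protections exist: voluntary participation, withdrawal without effect on employment, restricted data access, aggregate reporting and de-identified transcripts. These bear on fear of reprisal and protect the content, but they do not address the room or the visibility of attendance.

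Fifthly, any interview on hospital premises can be noticed, and snowball referral (section 2.2.6) already tells some colleagues about participation. So the disclosure added by this room is uncertain. It still differs in kind, because the person who may learn of attendance is a supervisor.

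Finally, an article may leave operational detail to a fuller document. That would answer a complaint that venue rules are missing. It does not answer this point, because the article itself names the room.

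**Conclusion.** The point holds in a limited form. The plan permits a venue that works against its own aim of limiting power imbalance and social desirability bias, in interviews that ask nurses about management. Candour could suffer and attendance could become known to a supervisor, most plausibly where the office belongs to the nurse's own line supervisor. The venue is optional, the effect is restricted to qualitative interviews held there, and its size cannot be estimated from the document.

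The conclusion rests on two assumptions: that at least some interviews would use such an office, and that a supervisor's space can affect what nurses are willing to say. The plan's own safeguard rests on a similar premise about authority. The change is worth making because it removes an avoidable source of a bias that the plan names, and candour lost in an interview cannot be restored in analysis.

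**What to change.** Under Interview mode and approximate duration, delete the supervisor's office. Specify a private room not controlled by the participant's line management, with the meeting room already listed as the example. No other section needs to change.

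The cost is one phrase and the small effort of booking a neutral room. The article states that recruitment has not begun, so the change can apply to every interview.

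Letting the nurse choose the place and recording the location of each interview would be useful extras. They are optional, and the plan is not wrong for lacking them.
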